### Polymerase chain reaction (PCR)

Bacterial and Viral DNA extraction will be performed according to Boom et al.[38] Bacterial PCR will be performed as described by Ashimoto et al.[39] in and Saiki et al.[40] For *P. gingivalis*, *T. forsythia*, *E. corrodens *and *C. rectus *a 50 μl of a reaction mixture containing 10.0 μl sample template, 5.0 μl of 10× PCR buffer (50 mM KCl, 10 mM Tris-HCl [pH 9.0 a 25°C], 1.5 mM MgCl_2 _and 0.1% of Triton^® ^X-100) o PROMEGA0.25 U of Taq DNA polymerase, 5.0 μl (0.2 Mm) of each of deoxyribonucleotides, 1.0 μl (2 μM) of the primer from the bacteria being investigated and 3.0 μl MgCl_2 _(1.5 mM), was used. For *A. actinomycetemcomitans*, *P. intermedia *y *P. nigrescens *the concentration of MgCl_2 _was 2.25 mM

The primers used will be those recommended by Ashimoto et al.,[39] positive and negative controls will be included for each bacterium, and a 1 Kb molecular weight marker. The sample will be replaced by 10.0 μl sterile distilled water in the negative control and 10.0 μl of DNA from the bacteria being investigated will be included in the positive control.

Samples will be amplified in a thermal cycler (MyCycler™ Termal Cycler, Bio-Rad). The PCR temperature profile for *P. gingivalis*, *T. forsythia*, *E. corrodens *and *C. rectus *included an initial denaturation step at 95°C for 2 min followed by 36 cycles of: denaturation step at 95°C for 30 s, a primer annealing step at 60°C for 1 min, an extension step at 72°C for 1 min and a final step of 72°C for 2 min. The temperature profile for *A. actinomycetemcomitans*, *P. intermedia *y *P. nigrescens *will included an initial step of 95°C for 2 min followed by 36 cycles of: 94°C for 30 s, 55°C for 1 min, 72°C for 2 min and a final step of 72°C for 10 min.

*P. gingivalis *ATCC 33277, *C. rectus *ATCC 33238, *T. forsythia *ATCC 43037, E. corrodens ATCC 23834, *A. actinomycetemcomitans *ATCC 29522, *P. intermedia *ATCC 25611 y *P. nigrescens *ATCC 33563 reference strains will be used. *P. gingivalis *will be identified by the presence of an amplified product in the 404 base pair (bp) band, *C. rectus *by an amplified product in the 598 bp band, *T. forsythia *in the 641 bp band, *E. corrodens *in the 688 bp band, *P. intermedia *in the 575 bp band and *P. nigrescens *in the 804 bp band. The primers used will be the ones described by Ashimoto et al.[39] were selected with the help of the Ribosomal database Project (RDP) program.

A nested PCR for HCMV will be used to determine the subgingival viral presence. HCMV PCR conditions and primers will be selected as published by Parra et al.[41] Positive control - DNA extracted from HCMV Towne strain and negative control will be used during the experiments. A band of 123 base pair will represent a HCMV positive isolation.

Bacterial and viral PCR products will be electrophoretically fractioned at 4 V/cm in 1.5% agarose gel in TAE buffer (Tris acetate-EDTA) stained with cyber green and visualised on a transilluminator under 300 nm ultraviolet light.

The subgingival microbiota composition of the patients will be determined at baseline and at three months after study inclusion and will be analyzed as other independent microbial risk factor. The effect of periodontal treatment on subgingival microbiota composition will be also determined.

### Physical and anthropometric measurements

All physical and anthropometric measurements will be performed in the morning before breakfast. Participants will be wearing light clothes and no shoes during examination.

*Weight*: The weight scale will be placed in a hard-flat surface and properly calibrated before each measurement. All measurements will be taken with the patient standing without support on the centre of the scale with their weight distributed evenly in both foot.

*Height*: will be measured using a metric tape with the patient standing against the wall with their head in the Frankfort plane.

*Body Mass Index (BMI)*: will be calculated using the weight (kg) divided by the second power of the height (meters).

*Waist*: the circumference of the abdomen at its narrowest point will be measured using a metric tape against the skin of the participants. All measurements will be taken perpendicular to the long axis of the trunk, between the lower costal border and the top of the iliac crest.

*Heart rate*: calculated using the R-R interval in the electrocardiogram with the patient in the supine position after a 5-minute rest.

*Blood pressure (BP)*: BP will be taken using a mercury sphygmomanometer on the right arm, with the patient comfortably seated, after a 5-minute rest[42].

### Assessment of vascular function

All the assessments of vascular function will be performed in the morning, in a temperature controlled room, with participants required to fast for at least 8 hours. Flow-mediated, endothelium dependent vasodilatation of the brachial artery (FMD) will be measured by the technique described by Celermajer et al.[28] using the guidelines reported by Coretti et al.[43] The ultrasound image of the right brachial artery will be measured longitudinally 5-10 cm above the antecubital fossa by a 2D high-resolution (Siemens SG-60, USA) ultrasound device, using a 7.5 MHz linear array transducer. Ultrasound procedures will be executed with the subject resting quietly in supine position for at least 10 minutes. All measurements will be taken at end-diastole guided by the electrocardiogram. The baseline diameter of the brachial artery will be measured from the anterior to the posterior intima/lumen interface at three points located at a predetermined distance, the mean diameter of the brachial artery will be calculated as the average of the three measures. After the baseline measurement, a pneumatic tourniquet positioned around the right arm will be inflated to at least 50 mm Hg above the systolic pressure for at least five minutes. A rapid release of the cuff will induce reactive hyperemia and shear stress on the endothelium, leading to endothelium-dependent vasodilatation, mainly due to the increase of free cytosolic Ca^2+ ^concentration with subsequent activation of endothelial Nitric Oxide Synthase (eNOS) and release of NO to the vascular smooth muscle[43]. FMD will be calculated as the percentage of change in the diameter of brachial artery measured 45-60 s after cuff release in relation to the baseline measure (FMD%). After 10 minutes of rest, sublingual administration of 25 μg of nitroglycerin will be used to measure the endothelium-independent vasodilatation.

### Statistical analysis

All statistical analyses will be performed using the intention-to-treat principle unless stated otherwise. A P of 0.05 will be used as a cutoff for statistical significance. The primary outcome (difference on endothelium-dependent brachial artery FMD at baseline and three months after randomization) and the secondary outcome (hs-CRP, glucose, blood lipid profile, and HOMA index) will be analyzed using repeated measures ANOVA for continuous variables. Differences in proportions in outcomes between the treated group and the control group will tested for statistical significance by χ2-test or Fisher exact test if applicable.

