#### - Secondary outcomes

Secondary outcomes of this study are hs-CRP and glucose serum levels, blood lipid profile, and HOMA index [Time Frame: Baseline, 24 h and 12 weeks after treatment].

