### Blood samples

Venous blood samples will be withdrawn from the antecubital vein in fasting conditions (8 to 10 hours). Blood samples will be collected using three vacutainer tubes, one dry, one with EDTA and another with sodium heparin. One 1000 uL aliquote of the EDTA blood sample will be used for Complete Blood Count (CBC). All remaining samples will be centrifuged at 1500 rpm during 10 minutes to extract the plasma and serum. Plasma obtained during visits II, IV and V will be stored in Eppendorf vials at -70°C until the end of the study for the analysis of cytokines by Multiplex^®^, hs-CRP and insulin. Serum samples will be immediately analyzed for measurement of glucose and lipid profile.

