### Biochemical markers

Biochemical tests will be performed in the Microbiology and Immunology Laboratory, from the Universidad del Valle (Cali, Colombia) and other private certified Clinical Laboratory.

*Plasma glucose levels*: glucose measurement will be performed using enzymatic-colorimetric techniques (Selectra, Merck).

*Lipid profile*: High-density lipoproteins cholesterol (HDL-C), total cholesterol (TC) and triglycerides will be determined by enzymatic-colorimetric techniques (Selectra, Merck). Low-density lipoproteins cholesterol (LDL-C) will be calculated using the Friedwald equation: LDL-C = TC-(HDL-C+TG/2.2).

*High sensitivity C-Reactive Protein (hs-CRP)*: the fasting plasma hs-CRP concentrations will be analyzed using a solid-phase, chemiluminescent immunometric assay (Immulite 1000, Siemens).

*Complete Blood Count (CBC)*: CBC will be performed using an automated analyzer (Advia 60, Siemens).

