### Luminex multiplex assay for measurement of cardiovascular risk biomarkers

Cardiovascular risk biomarkers will be determined on plasma samples using the Luminex-200 system (Luminex Corporation). This system allows measuring up to 200 proteins simultaneously in a small sample volume (25-50 μL). MILLIPLEX™ MAP biomarker panel will be used to determine the following cardiovascular risk biomarkers: MMP-9, MPO, PAI-1 (total), sE-Selectin, sICAM-1, sVCAM-1, hs-CRP, fibrinogen, haptoglobine, amyloid A and amyloid P.

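### hs-CRP, HOMA and triglycerides share FMD's repeated measures ANOVA; a log-scale, baseline-adjusted analysis would keep more power if these markers are skewed

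*Protocol article*

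**What the plan says.** Under Secondary outcomes: "Secondary outcomes of this study are hs-CRP and glucose serum levels, blood lipid profile, and HOMA index", at baseline, 24 h and 12 weeks. Under Statistical analysis, the FMD outcome and these markers share one sentence and one method: "the secondary outcome (hs-CRP, glucose, blood lipid profile, and HOMA index) will be analyzed using repeated measures ANOVA for continuous variables". The threshold is common to all: "A P of 0.05 will be used as a cutoff for statistical significance". The section mentions no transformation, no baseline covariate and no stratification factor, although the randomisation section stratifies by gender and smoking status.

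hs-CRP appears under two laboratory methods. Biochemical markers gives it its own paragraph: "the fasting plasma hs-CRP concentrations will be analyzed using a solid-phase, chemiluminescent immunometric assay (Immulite 1000, Siemens"). The Luminex section lists it again as one of eleven panel analytes: "MMP-9, MPO, PAI-1 (total), sE-Selectin, sICAM-1, sVCAM-1, hs-CRP, fibrinogen, haptoglobine, amyloid A and amyloid P".

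**The concern.** One normal-theory method covers FMD, which is a percentage change in diameter, and also concentrations and an index that can only be positive. The standard HOMA index is built from the product of fasting glucose and insulin, so variation in the two multiplies. hs-CRP and triglycerides can plausibly range over several-fold differences between patients. If the distributions have a long right tail, a few high values dominate both the mean and the residual variance, and a proportional fall shared by most patients is hard to see.

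At stake is the ability to detect an effect on the inflammatory and metabolic secondary outcomes. The Sample size section sizes the trial on FMD alone, so nothing was planned to protect power for these markers.

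**Working it through.** **The plan's own figure.** There is none to reproduce here. The only power statement concerns FMD; no SD, effect or power is given for hs-CRP, HOMA or triglycerides.

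**Inputs from the protocol.** 49 patients per group, 15% loss, two-sided 5%. Completers per arm: 49 × 0.85 = 41.65, taken as 42.

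**Inputs that are assumptions.** Lognormal marker; SD on the log scale (s) of 0.5, 0.8, 1.0 or 1.2; correlation (ρ) between log baseline and log follow-up of 0.6; geometric mean ratio of 0.7 (a 30% reduction) or 0.6 (a 40% reduction).

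**Tests compared.** With two time points, the group-by-time test of a repeated measures ANOVA is the t test on change. Three analyses were compared: change in the measured value, change in the log value, and log follow-up adjusted for log baseline (ANCOVA). The planned analysis has three time points, so this is a simplification.

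**Closed form on the log scale.**
- SD of log change = s√(2(1 − ρ)) = 0.894s.
- Residual SD of log ANCOVA = s√(1 − ρ²) = 0.80s.
- Approximate power = Φ(|ln ratio| / (SD × √(2/42)) − 1.96), with √(2/42) = 0.2182.

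Example at s = 0.8 and ratio 0.7, where |ln 0.7| = 0.3567:
- Log change: SD 0.7155, standard error 0.1561, 0.3567/0.1561 = 2.285, power Φ(0.325) ≈ 63%.
- Log ANCOVA: SD 0.640, standard error 0.1397, 0.3567/0.1397 = 2.554, power Φ(0.594) ≈ 72%.

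The t distribution lowers each by about one point, in line with the simulations below.

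**Simulated power, 30% reduction, ρ = 0.6** (6,000 to 20,000 trials per setting; a range shows variation between repeat runs):

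| log-SD | untransformed change | log change | log ANCOVA |
|---|---|---|---|
| 0.5 | 83–84% | 95% | 98% |
| 0.8 | 36–38% | 61–62% | 71% |
| 1.0 | 22% | 43–44% | 51–52% |
| 1.2 | 13–14% | 31–33% | 38–39% |

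The step from the second to the third column is the effect of scale alone, about 11 to 25 percentage points. The last column adds the gain from baseline adjustment.

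**40% reduction, log-SD 0.8/1.0/1.2.** Untransformed change 61/36/22%, log change 91/73/56%, log ANCOVA 95/82/66%.

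**Sensitivity to the correlation, 30% reduction, untransformed against log change, log-SD 0.5/0.8/1.0/1.2.**
- ρ = 0.5: 76/32/19/13% against 90/53/36/27%.
- ρ = 0.7: 91/47/27/16% against 99/75/55/41%.

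The log scale has the higher power in every setting.

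**Type I error.** With no true effect, the untransformed analysis rejects in 3.9 to 4.8% of trials with 42 per arm (ρ of 0.5 and 0.7), so it is slightly conservative.

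**The case against.** **Scale.** A reader might infer that the protocol commits to untransformed values. It does not: no scale is stated, and a repeated measures ANOVA of log values would satisfy the sentence. The article condenses a fuller document, and the analysis scale is a detail often left to the analysis plan. This stands, so the point is a better choice to write down and not a proven error.

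**Skewness and size.** The document gives no spread for these markers, and its exclusions (diabetes, autoimmune, liver, renal and cardiovascular disease among them) could narrow it. Lognormal data with a multiplicative effect favour the log analysis by construction. Both remarks are fair, and the figures are therefore conditional. It is also true that the log scale does not rescue every case: for a 30% reduction at log-SD 0.8 or more, even log ANCOVA stays below 80% at ρ = 0.6. Much of the shortfall there comes from sample size.

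**Two assays.** A reader might infer that the duplicate hs-CRP measurement leaves a free choice of result. That goes too far. Visit II and Visit V list hs-CRP apart from the cytokine panel. Blood samples does likewise: plasma is "stored in Eppendorf vials at -70°C until the end of the study for the analysis of cytokines by Multiplex", with hs-CRP and insulin named separately. Biochemical markers gives hs-CRP its own analyser beside glucose and lipids. The natural reading is that the chemiluminescent result is the endpoint. Even a free choice between two independent tests would give at most 1 − 0.95² = 9.75%, and two assays of one analyte should lie much nearer 5%. What remains is that no sentence says so outright.

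**Conclusion.** The point holds as a low-severity recommendation on the choice of analysis. If the markers are roughly lognormal with log-SD 0.5 to 1.2 and a baseline correlation of 0.6, untransformed change has about 13 to 84% power for a 30% reduction, log change about 31 to 95%, and log ANCOVA about 38 to 98%. The direction does not depend on the particular log-SD, correlation or effect tried; the size does. If the markers turned out close to symmetric, the scale would matter little, though adjusting for baseline would still help.

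The calculations do not support a claim of false-positive inflation from the planned ANOVA, and the text does not support a claim that it fixes the raw scale. The primary FMD analysis is not touched by this point.

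**What to change.** In Statistical analysis, separate hs-CRP, HOMA and triglycerides from FMD. State that they are analysed after log transformation, adjusted for the log baseline value and the randomisation strata (gender, smoking status), with geometric mean ratios and 95% CI at 24 h and 12 weeks.

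Add one clarifying sentence: the chemiluminescent hs-CRP measurement in plasma is the secondary endpoint, and the multiplex hs-CRP is supportive. The Secondary outcomes wording speaks of serum levels, so the specimen should be named at the same time.

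The cost is wording only, with no new data, visits or samples. Results for these markers become ratios, which some clinical readers find less familiar than differences in mg/L; medians by arm and visit can be shown alongside. Since plasma for hs-CRP and insulin is stored until the end of the study, the wording for hs-CRP and HOMA can be settled before those results exist.

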#### - Visit II

baseline endothelium-dependent brachial artery flow-mediated dilatation and anthropometric parameters (weight, height, and abdominal circumference). A fasting blood sample will be obtained to determine glucose, insulin, hs-CRP, lipid profile, and a pro-inflammatory cytokine panel by Multiplex^®^.

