### Sample size

The primary outcome FMD was selected as the critical variable to calculate the sample size. 49 patients (98 in total) in each group are required to have an 80% chance of detecting as significant (at the two sided 5% level) a 1% difference between the two groups in the mean FMD, with assumed standard deviation of 2.6 and a planned 15% rate of missing patients on the follow up.

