### Randomization, allocation concealment and blinding

Subjects will be randomized into one of two groups: 1) treatment group (one stage full-mouth disinfection), and 2) control group (conventional adult prophylaxis). Randomization will be stratified on the basis of gender (male or female), and smoking status (*current smokers*: subjects who reported regular smoking of one or more cigarettes a day for at least one year; *non-smokers*: never smoke and former smokers who had stopped smoking for at least 12 months). The sequence will be generated using a random number generator in a computer by an independent researcher not involved in the interventions or measuring the clinical variables. Random permuted blocks with a size of four patients will be selected. Sequentially numbered, opaque, sealed envelopes (SNOSE) were developed for the implementation of the random sequence.

On the treatment day, a trained nurse will open the corresponding numbered envelope at the Cañaveralejo Health Center or at the dental clinics Universidad del Valle. The patient's group allocation will be given to the periodontist to perform the corresponding intervention. Due to the nature of the interventions, it is no possible to blind study participants and periodontists for the treatment protocol. Outcome evaluators and data analysts will be blinded to the group assignment. Detailed instructions on methods to maintain the blind will be given to the researchers, health care providers and outcome evaluators. Furthermore, these instructions were reinforced in bimonthly meetings with the personal involved in the study and detailed in the operations manual.

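### The primary analysis most naturally treats baseline FMD as a repeated outcome and names no 12-week contrast; a baseline-adjusted 12-week comparison is more efficient, by an amount set by an unstated correlation

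*Protocol article*

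**What the plan says.** - **Outcome.** The Primary outcome section defines the outcome as the difference in FMD at baseline and three months, with a time frame of baseline, 24 hours and 12 weeks.
- **Analysis.** The Statistical analysis section says that this outcome and the secondary outcomes "will be analyzed using repeated measures ANOVA for continuous variables". It names no effect (group, time or group-by-time) as the test, no 12-week contrast and no covariates.
- **Timing of baseline.** Visit II covers "baseline endothelium-dependent brachial artery flow-mediated dilatation and anthropometric parameters". Randomisation follows at Visit III, so baseline FMD precedes allocation.
- **Strata.** "Randomization will be stratified on the basis of gender (male or female), and smoking status" (Randomization, allocation concealment and blinding). The analysis section does not mention these factors either way.
- **Sizing.** The Sample size section targets "a 1% difference between the two groups in the mean FMD", "with assumed standard deviation of 2.6", tested "at the two sided 5% level", with 80% power and "a planned 15% rate of missing patients on the follow up". It gives no baseline correlation and does not say whether 2.6 is the SD of a single FMD value or of a change.

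**The concern.** Treatment cannot affect a value measured before randomisation. Entering that value as a level of the outcome, instead of as a covariate, has two consequences.

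First, several tests fit the stated method. With baseline and 12 weeks only, the group-by-time test is the same as a two-sample test on change scores. With all three visits, the group-by-time test is an omnibus test on two numerator degrees of freedom, and it also responds to whatever happens at 24 hours. The section does not say which of these decides the trial.

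Second, the change score gives baseline a fixed weight of one. Unless r is 1 this is too much, and it adds noise. ANCOVA estimates the weight from the data. Baseline FMD, gender and smoking status are all recorded anyway, so precision would be lost for no saving. Power is already short on the Sample size section's own inputs.

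**Working it through.** **The plan's own figure.** Stated inputs: difference 1, SD 2.6, two-sided 5%, 80% power, 15% missing.

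n per arm = 2(1.960 + 0.842)² × 2.6² / 1² = 106.1, so 107. Allowing for loss: 107 / 0.85 = 125.9, so 126 per arm. The stated 49 is not reproduced. This is a separate problem, but it sets the starting level of power below.

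**Inputs for the comparison**
- Evaluable per arm: 49 × 0.85 = 41.65, taken as 42.
- Difference 1 and two-sided 5%, from Sample size.
- r: not in the document; assumed from 0.3 to 0.9.
- 2.6: first taken as the SD of one FMD value, then as the SD of the change, because the document does not say which.

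**Formulas** (σ is the SD of one value, equal at both visits)
- Change score: SD = σ√(2(1−r)).
- Baseline-adjusted 12-week comparison: SD = σ√(1−r²).
- Variance ratio, adjusted to change: (1−r²) / (2(1−r)) = (1+r)/2, below 1 for every r below 1.
- Power: noncentral t with noncentrality 1 / (SD × √(2/42)).

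**Reading A: 2.6 is the SD of one value**

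| r | Variance ratio | SD, change | SD, adjusted | Power, change | Power, adjusted |
|---|---|---|---|---|---|
| 0.3 | 0.65 | 3.08 | 2.48 | 31% | 45% |
| 0.5 | 0.75 | 2.60 | 2.25 | 41% | 52% |
| 0.7 | 0.85 | 2.01 | 1.86 | 61% | 68% |
| 0.8 | 0.90 | 1.64 | 1.56 | 79% | 83% |
| 0.9 | 0.95 | 1.16 | 1.13 | 97% | 98% |

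A comparison of 12-week values that ignores baseline has 41% power throughout. Below r = 0.5 the change score is therefore worse than not using baseline at all.

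**Reading B: 2.6 is the SD of the change.** The change-score test has 41% power whatever r is. The adjusted SD is 2.6√((1+r)/2), which is 2.10, 2.25, 2.40 and 2.53 at r = 0.3, 0.5, 0.7 and 0.9. Power is then 58%, 52%, 47% and 43%.

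**Three-visit group-by-time test** (Reading A, equal correlation between visits, r = 0.5, noncentral F). Power is 33% if the 24-hour difference is +0.5, 42% if it is 0 or +1, and 89% if it is −1. In the last case most of the signal comes from the swing between 24 hours and 12 weeks, not from the 12-week difference.

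**Strata.** If gender and smoking status explain an assumed 2% to 10% of the residual variance, they add roughly 1 to 5 points of power. The document gives no figure for this.

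**The case against.** **The planned method is valid.** This stands. Under randomisation the group-by-time test is unbiased with correct type I error. The point concerns efficiency and naming the test.

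**The gain rests on an unknown r.** This stands as to size. On Reading A the advantage is about 14 points at r = 0.3, about 4 at 0.8 and under 1 at 0.9. The direction against the change score does not depend on r. Against the three-visit omnibus test even the direction can vary: that test can match or exceed the adjusted comparison when r is high or the 24-hour effect has the opposite sign. It then answers a different question from the 12-week difference.

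**Stronger readings that the document does not support**
- *The plan ignores its strata.* A reader might infer this from the missing covariates. The article is condensed and silent, and covariates may be set in a fuller plan. Omitting prognostic strata would make standard errors conservative; it would not invalidate the test.
- *The test is the group main effect averaged over visits.* Its power would be only about 11% at r = 0.5 with an effect at 12 weeks only, and about 30% with the full effect already present at 24 hours. No section names that test, and defining the outcome as a difference between baseline and three months points to change.
- *Adjustment would restore the planned power.* With 42 evaluable per arm and Reading A, it reaches 80% only if r is about 0.78 or more.

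**Conclusion.** The point holds as a recommendation on efficiency and clarity. The stated analysis most naturally treats a pre-randomisation value as an outcome level and leaves the deciding contrast unnamed. Adjusting for baseline removes a fraction (1−r)/2 of the variance of the change-score test: 35% at r = 0.3, 25% at 0.5, 15% at 0.7, 5% at 0.9. In power, with 42 per arm, that is about 7 to 14 points for r from 0.3 to 0.7 if 2.6 is the SD of one value, and less above that. If 2.6 is the SD of the change, the gain runs from about 17 points at r = 0.3 to about 2 at 0.9.

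These sizes assume equal SDs at both visits, a true difference of 1 and 15% loss. Both r and the meaning of the SD are assumptions. Nothing here shows the planned test to be biased or the strata to have been rejected. The change should be made because it costs so little.

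**What to change.** Replace the repeated measures ANOVA wording for the primary outcome with, for example:

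> The primary comparison is the between-group difference in FMD at 12 weeks, estimated by ANCOVA (or by the 12-week contrast of a mixed model of the post-baseline visits) adjusted for baseline FMD, gender and smoking status.

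Use the same form for hs-CRP, glucose, lipids and HOMA, each with its own baseline value. Including gender and smoking status matches the stratified randomisation and probably adds a small further gain.

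The cost is one sentence and a few degrees of freedom; every variable is already collected. Separately, state whether 2.6 is the SD of a single value or of a change, and reconcile the 49 per arm with its own inputs. The change of model does not do that.
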